### Methods for additional analyses (e.g., subgroup analyses) {20b}

Not applicable. No subgroup analyses are planned. Significant interaction effects will be used to suggest a differential effect of treatment across different patient groups.

### Methods in analysis to handle protocol non-adherence and any statistical methods to handle missing data {20c}

We perform statistical analysis on the complete case. The complete case is that all the data required for this study protocol are complete and there are no missing cases in order to be included in the final statistical analysis. The premise of this RCT is that it does not violate the treatment principles of the patient's disease and does not imply or modify the patient's treatment intention. The experiment respects the treatment willingness of each enrolled patient.

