#### Secondary outcomes

The occurrence time of postoperative RVF.The occurrence time of RVF after stoma closure.Postoperative complications, such as anastomotic leakage, chylous leakage, and intestinal obstruction.Postoperative serological test indexes, such as FSH, LH, E2, CEA, and CA199.Others about evaluating surgical methods, such as the duration of the operation, quality of life, abnormal discharge in the vagina.

The score of a functional assessment of cancer therapy (FACT) system will be used to evaluate the patient’s quality of life.

All data about the outcome will be collected according to the follow-up timepoint in Table 1. Measurement data between the two groups will be analyzed with the *t*-test and rank-sum test, while categorical data will be analyzed with *χ*^2^ test. The duration time will be recorded as mean ± standard deviation, and the incidence data will be recorded as median (first quartile, third quartile). The significance level used for statistical analysis will be two-sided with confidence intervals at the 95% level. All results will be applied to analyze the reliability of the new operation method, and to explore whether this new operation method will cause changes in the related complications, female hormones, affect the effect of the operation, and quality of life.

**Table 1 Tab1:** Schedule of enrolment, intervention, and assessments

Timepoint	Screening	Baseline	Intervention		Follow-up(months)											
			**Before**	**After**	**0**	**3**	**6**	**9**	**12**	**15**	**18**	**21**	**24**	**36**	**48**	**60**

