### Sample size {14}

Female patients with low and medium rectal cancer in the Department of Colorectal Surgery, Fujian Medical University Union Hospital, from April 2020 to March 2023 are selected as the research participants. It is assumed that the RVF of the study group is the same as that of the control group. According to previous research results and relevant literature reports, the incidence of RVF of the control group and the test group was set at 9.9%, the non-inferior margin value was set at 15%, the test level was set at 0.05, and the power was set at 0.8 [1, 2]. The sample size was calculated by SPSS24.0 software as follows: *N* = 115, and each group needed 115 people. We assume that 20% of patients would be lost to follow-up, and 144 would need to be enrolled.

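### The complete-case rule drops women with known RVF status from the primary analysis when any other protocol item is missing, and the 20% allowance does not budget for this.

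*Protocol article*

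**What the plan says.** Section {20c} of the protocol article bases the analysis on complete cases. It defines them by the patient's whole record, not by the endpoint being analysed: "The complete case is that all the data required for this study protocol are complete and there are no missing cases". It makes this a condition that a woman must meet "in order to be included in the final statistical analysis". No section sets a separate rule for RVF, the primary outcome.

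The Secondary outcomes section says what is required: "All data about the outcome will be collected according to the follow-up timepoint in Table 1". Table 1 marks 13 follow-up rows at each of 11 visits (months 3, 6, 9, 12, 15, 18, 21, 24, 36, 48 and 60). The rows include RVF, three complications, five blood tests, vaginal discharge and quality of life.

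Two other sections work in the same direction. Concomitant care {11d} takes dropouts and patients with other fatal complications out of the analyses. Statistical methods {20a} leaves out the data of patients who fall away.

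Sample size {14} states that "each group needed 115 people" and continues: "We assume that 20% of patients would be lost to follow-up, and 144 would need to be enrolled". Trial design {8} and section {20a} describe the trial as non-inferiority.

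**The concern.** A rule on missing data should ask whether the endpoint being analysed is known. This one asks whether everything is known. A woman with an RVF recorded at month 6 would not count as an event if her CA199 at month 36 were missing. A woman followed without RVF would also disappear for the same reason.

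What is lost is observed primary-endpoint data, and the loss depends on what happens after randomisation. Women with complications may attend less regularly, so RVF cases may be lost preferentially. Removing failures from both arms tends to pull the difference towards zero, which in a non-inferiority comparison favours the conclusion sought. Events are few to begin with: at the assumed 9.9%, 144 women yield about 14 RVFs (0.099 × 144 = 14.3). The rule also removes women whom the sample size made no provision to lose.

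**Working it through.** **1. The plan's own figure.** 115 / (1 − 0.20) = 143.75, rounded up to 144. This reproduces the stated enrolment. The 20% is described as loss to follow-up. If that loss occurs as assumed, 144 × 0.80 = 115.2 remain, so nothing is left for women who stay in follow-up but have an incomplete record.

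**2. Share of women complete.** The document gives no rate of missed visits, so per-visit completeness q is an assumption, shown over a range. If visits are missed independently, the share complete at all 11 visits is q^11. The counts take 144 as the starting number.

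| q | q^11 | complete, of 144 | complete if 20% are also lost (144 × 0.80 × q^11) |
|---|---|---|---|
| 99% | 0.895 | 129 | 103 |
| 98% | 0.801 | 115 | 92 |
| 97% | 0.715 | 103 | 82 |
| 95% | 0.569 | 82 | 66 |

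If the whole 20% could be spent on incomplete records, q would have to be at least 0.80^(1/11) = 0.980.

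**3. Clustered missingness.** If some women miss many visits and most miss none, more women are complete. A beta-binomial model with intraclass correlation 0.3 gives 91.3% complete at q = 98% and 79.5% at q = 95%.

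**4. Power.** The inputs are 9.9% RVF in both arms, a margin of 15 (read as percentage points), power 0.8 and a two-sided 95% interval.

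- Required n per arm = 2 × 0.099 × 0.901 × (1.960 + 0.842)² / 0.15² = 62.3, rounded up to 63.
- Power at n per arm = Φ(0.15 / √(2 × 0.099 × 0.901 / n) − 1.960).
- If 144 is per arm, q = 95% leaves 82 per arm and power of about 0.895.
- If 144 is the total (72 per arm), q = 95% leaves 41 per arm and power of about 0.62. At q = 98%, 58 per arm remain and power is about 0.77.

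The arithmetic 115/0.8 points to 144 per arm, because 115 is a per-group number, but section {14} does not say so.

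**5. Direction of the bias (illustration on assumed attendance).** Let the true risks be 9.9% and 24.9%, a difference of 15 points, exactly at the margin. Suppose women with RVF complete 95% of visits (share complete 0.569) and women without RVF complete 98% (0.801), in both arms alike.

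- Arm at 9.9%: 0.099 × 0.569 / (0.099 × 0.569 + 0.901 × 0.801) = 0.0563 / 0.7780 = 7.2%.
- Arm at 24.9%: 0.249 × 0.569 / (0.249 × 0.569 + 0.751 × 0.801) = 0.1417 / 0.7432 = 19.1%.

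The complete-case difference is 11.8 points instead of 15.0. A larger sample would not correct this.

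**The case against.** The strongest reply is that the size of the problem is not in the document. A reader might infer that the 20% allowance cannot hold. That does not follow: at 98% completeness per visit with independent misses, 80% of women are still complete. With clustering, roughly the same holds at 95%, provided other losses are small. What stands is that the allowance was made for something else.

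A reader might also infer that power must collapse. The stated non-inferiority inputs do not support this. They require about 63 per arm, so with 144 per arm every row of the table in the working keeps at least 80% power, even the last column at 66. The planned 115 is therefore not a power threshold on those inputs. The risk to power is real only if 144 is the total.

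A third tempting reading is that the result would apply only to five-year survivors. Table 1 runs to month 60, but Trial design {8} places the trial in April 2020 to March 2023. The article does not fix when the final analysis is done, nor whether visits after a death count as required data. The defect is the same at any cut-off. Nor is it sound to treat every cell of Table 1 as an independent chance of a missing value. The two RVF-timing rows follow from RVF occurrence and stoma closure, and the five blood tests share a visit and would largely go missing together.

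Finally, imputation models and similar detail belong in an analysis plan that may exist but is not shown. That is fair. The present point does not rest on an omission, because the inclusion rule itself is written down.

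**Conclusion.** The rule is wrong as written and should be changed, because it decides who enters the primary analysis. On its literal reading, known RVF outcomes are discarded for missing secondary items, and the exclusions in {11d} and {20a} add to the selection after randomisation. The main harm is bias, possibly towards no difference. The illustrated fall from 15.0 to 11.8 points shows the mechanism under assumed attendance and is not a forecast.

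On numbers, the supportable statement is limited. The 20% allowance does not cover this rule, and the target of 115 is unlikely to be kept unless follow-up is almost complete: about 98% per visit with independent misses and no other loss, or less if misses cluster. Whether power falls below 80% depends on whether 144 is per arm or total, which section {14} leaves unclear.

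**What to change.** - In {20c}, delete the condition that all protocol data be complete.
- Amend the matching exclusions in {11d} (dropouts, other fatal complications) and {20a} (data that fall away). Changing {20c} alone would leave them in force.
- Analyse RVF in all randomised women as allocated, using each woman's RVF follow-up to RVF, death or last contact, whatever else is missing.
- Analyse each secondary outcome with the data available for that outcome.
- Add one simple sensitivity analysis for unknown RVF status, for example worst-case assignment by arm.

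The cost is a change of wording in three sections and a little more analysis work. No new data are needed.

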### Plans to give access to the full protocol, participant-level data, and statistical code {31c}

The original data will be published and shared in the Chinese Clinical Trial Registry (ChiCTR, https://www.chictr.org.cn/searchproj.html). And accept the supervision of the center.

## Oversight and monitoring

### Composition of the coordinating center and trial steering committee {5d}

In order to control the quality of the clinical trial, the whole process of the trial will be conducted under the supervision of a qualified clinical trial expert at Fujian Medical University Union Hospital. The qualified clinical trial expert of Fujian Medical University Union Hospital will conduct the data monitoring. When problems occur in the trial, the expert has the right to make the final decision to terminate the trial if necessary. Any changes will be notified in writing to all participants in the trial after approval by the ethics committee. The principle investigator will be fully responsible for conducting the trial and will make any final decisions.

### Composition of the data monitoring committee, its role and reporting structure {21a}

In order to control the quality of the clinical trial, the whole process of the trial will be conducted under the supervision of a qualified clinical trial expert at Fujian Medical University Union Hospital. The qualified clinical trial expert of Fujian Medical University Union Hospital will conduct the data monitoring. When problems occur in the trial, the expert has the right to make the final decision to terminate the trial if necessary. Any changes will be notified in writing to all participants in the trial after approval by the ethics committee. The principle investigator will be fully responsible for conducting the trial and will make any final decisions.

### Adverse event reporting and harms {22}

Risks greater than routine operation incurred through participating in this trial are not anticipated. As a result, no discomfort or adverse events are anticipated for this study. However, in the study debrief form, participants will be provided with routes for providing feedback for seeking support. Specifically, participants will read the following text: “If you have any issues that have arisen through participating in this study, you may wish to contact the research assistant and obtain a clinical management plan from the clinician.” All adverse events (reported and observed) will be reported to the Research Ethics Committee and recorded by the research team, with respect to any of the following types of harm occurring in the study, and the likelihood, severity, and consequence of those harms occurring.

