## Interventions

### Explanation for the choice of comparators {6b}

This trial will compare the efficacy of preventing RVF. Compared to the control group, the experimental group would add a step to an operation of packing with a dislocated fat flap containing ovarian vascular pedicle anterior. The operations will be performed by the same clinic doctor of the trial at Fujian Medical University Union Hospital. It has the advantages of not being easily perceived by the patient and a higher feasibility of operation.

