### Intervention description {11a}

#### Group A (experimental group)

All operations will be performed according to the principle of TME radical resection in rectal cancer surgery. The anterior rectal wall of about 1 cm distal to the anastomosis will be dislocated.Before the rectal anastomosis, the researcher would expose one side of the ureter (usually the left side), dislocate the fat flap containing ovarian vascular pedicle to avoid damage of the ureter, and dissect ovarian vessels proximal to the kidney. After dislocating the fat flap, the size of the packing end would be 2 cm (width) × 4–5 cm (length) at least, with a 10–15 cm in total length, which would be measured by a thread during the operation. This length would ensure to pull-down to 5 cm below the anastomosis (Figs. 1, 2, and 3).After rectal anastomosis, a large amount of normal saline will be used to rinse the pelvic cavity. The liquid will be sucked up. The surface of the rectum and vagina will be dried with gauze.The fat flap containing ovarian vascular pedicle will be flipped downward and packed between the anastomotic stoma and vagina (9 o’clock to 3 o’clock of the outer wall of the rectum in lithotomy position), then fixed with medical fibrin glue. (Fig. 4)

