**Fig. 1 Fig1:**
[figure not shown]
Separate the ovarian vessels and protect the ureter

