### Confidentiality {27}

This study intends to sign a clinical trial informed consent prior to surgery to inform patients of their relevant rights and interests. Patients’ data included in this study will be confidential, patient specimens will be identified by study numbers rather than patient names, and patient information will not be disclosed to members outside the study team. No patient information will be disclosed when the study results are published. All patients in the experimental group have ovarian failure, and the study would not increase the additional risk and cost of patients, while the control group only has radical rectal cancer surgery, which would not increase the additional risk and cost of patients. We will protect the privacy of participants’ personal medical information as required by law. The staff in this study is also bound by this agreement.

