#### Samples

It is expected that the total number of samples would reach 80–100. The cases and controls were grouped according to the experimental protocol, and mid-term experimental data would be collected to analyze the expected risks of intervention measures. When adverse events or other related complications occur, patients who consider adverse outcomes would be reported by the research team and analyzed to determine whether their adverse events are related to the trial, and the research team would fulfill their obligation to inform and respect the patient's right to know related content. In the case of mid-term analysis, if there is no statistically significant difference between the case group and the control group or there are more adverse complications in the case group compared to the control group, the trial can be considered for discontinuation and protocol modification can be carried out. If there are significant modifications during the implementation process, the main researcher shall write and sign a “protocol modification manual” and submit it to the ethics committee for approval before implementation.

In the study, if the analysis results have no clinical significance due to the number of cases, the experimental time will be extended. The interim analysis report will be publicly released by the research participants.

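### The no-added-risk statements contradict the protocol's own description of the flap step, and ureteral injury, the hazard it warns of, is not a named outcome and has no scheduled collection at operation

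*Protocol article*

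**What the plan says.** Two sections of the protocol article deny added risk. Adverse event reporting and harms (item 22) opens with "Risks greater than routine operation incurred through participating in this trial are not anticipated" and continues "As a result, no discomfort or adverse events are anticipated for this study". Confidentiality (item 27) says of the experimental group that "the study would not increase the additional risk and cost of patients".

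The intervention sections describe what that group receives in addition. Under the choice of comparators (item 6b), "the experimental group would add a step to an operation". Under Group A (item 11a), the surgeon exposes one ureter and is to "dislocate the fat flap containing ovarian vascular pedicle to avoid damage of the ureter, and dissect ovarian vessels proximal to the kidney". The Figure 1 caption reads "Separate the ovarian vessels and protect the ureter", and the Figure 2 caption says that the ovarian vessels are severed. Group B has only the standard resection.

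The interim analysis section (item 21b) says that data will be gathered to analyse the risks expected from the intervention. It allows discontinuation to be considered if "there are more adverse complications in the case group compared to the control group".

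On measurement, the secondary outcomes (item 12) give "Postoperative complications, such as anastomotic leakage, chylous leakage, and intestinal obstruction". Table 1 has a row for each of these three. Item 22 also commits the team to recording every adverse event and reporting it to the ethics committee.

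**The concern.** A protocol cannot hold both that participation adds no risk and that one arm undergoes an extra dissection in which a named organ must be protected. The difference between the arms is that step, so its hazards are the safety question of the trial. If the stated premise is that there are none, two things may follow. Those who write the participant information or judge relatedness may work from a wrong baseline. The one hazard the protocol itself identifies may also be left to whoever happens to report it, instead of being asked about in the same way in both arms. The interim decision compares complications between arms, and it needs to be clear which events enter that comparison.

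**Working it through.** No formula or sample size figure is at issue. The check is a comparison of the sections, plus a count of marks in Table 1.

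1. **Risk statement against procedure.** Items 22 and 27 claim no risk beyond the routine operation. Items 6b and 11a, with Figures 1 and 2, describe an added step for one arm only: ureter exposed, ovarian vessels dissected towards the kidney and severed, ureteral damage to be avoided. A warning to avoid an injury concedes that it is foreseeable. Item 27 sets the claim beside the fact that these patients have ovarian failure. If that is meant as the reason, it bears on ovarian function and not on the ureter or the vessels. The statements conflict.

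2. **Risk statement against interim plan.** Item 21b speaks of risks expected from the intervention, whereas item 22 says none are anticipated. These conflict as written.

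3. **Is ureteral injury a named outcome?** The named complications are three: anastomotic leakage, chylous leakage and intestinal obstruction. Ureteral injury appears neither in the secondary outcomes nor as a row of Table 1. The list is introduced as examples, so it is open.

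4. **Is there a harm list elsewhere?** Item 22 refers forward to types of harm, but none are listed in the text shown.

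5. **When are complications scheduled?** Table 1 has 12 follow-up columns: months 0, 3, 6, 9, 12, 15, 18, 21, 24, 36, 48 and 60. Each of the three complication rows carries 11 marks, and 12 − 11 = 1 column is empty. By position the empty column is month 0, and the columns before and after the intervention are empty too. The only outcome marked at month 0 is the duration of the operation. An injury caused by the added step would arise at or soon after surgery, before the first scheduled complication assessment.

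Together, steps 3 to 5 leave an operative ureteral injury to general adverse event recording, with no row, no listed harm type and no scheduled collection at the operation.

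**The case against.** The strongest reply is that harm capture is already provided for. The complication list is open, every adverse event is to be recorded with its likelihood, severity and consequence, and item 21b adds an assessment of whether events are related to the trial. Expecting no events does not cancel a duty to record them. Operation duration, hormones, vaginal discharge and quality of life are also collected, so the protocol does look for effects of the flap. The month 3 visit may look back to the operation. A journal article condenses the full protocol, and the harm list and the case report forms may carry these items.

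Much of this stands. A reader might infer that flap-specific harm is under-measured or will be missed. The documents do not establish that: ureteral injury is not pre-specified, which is different from not collected. Nor is the interim decision confined to the three tabulated complications; its wording is general.

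Other tempting inferences also fail:
- The possibility of discontinuation is a contingency, and planning for harm is compatible with not expecting it.
- Intraoperative bleeding in the discontinuation criteria (item 11b) is a general crisis example and is not tied to the flap.
- The longer operating time mentioned in the Discussion comes from a cited study of omentum packing, and operation duration is already an outcome here.
- Bleeding and pelvic infection can occur in either arm, so the lack of rows for them cannot be said to favour the flap in every case.
- The consent form is an additional file that is not shown. Item 26a says that risks are explained, so nothing visible shows that participants are told there are none.

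The reply does not remove the contradiction between items 22 and 27 and the described procedure. That is what the published text says, not a detail left to another document. Nor does it give the named hazard a scheduled assessment in Table 1.

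**Conclusion.** The point holds in a narrow form. Two statements, in items 22 and 27, are contradicted by the protocol's own account of the added step and by the interim section's reference to expected risks. The hazard that the protocol warns of is not a pre-specified outcome, and the complications that are named have no scheduled collection at the operation or at month 0.

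No size in events can be given. The documents state no rate of ureteral or vascular injury, and multiplying an assumed rate by the arm size would not show that an event goes unrecorded. The consequence is an incorrect stated risk profile and reliance on general reporting for operative harm. It is worth correcting because the correction is cheap; it does not undermine the primary comparison.

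The verdict assumes that the positions of the marks in Table 1 survived extraction (the count of 11 marks for 12 columns supports this), and that no harm list in the full protocol or case report forms already closes the gap.

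**What to change.** - Reconcile items 22 and 27 with items 6b and 11a and Figures 1 and 2 by replacing the no-added-risk wording with the foreseeable risks of the added step. Supply the list of harm types that item 22 announces.
- Check that the consent information, which is not shown, agrees with the corrected text.
- Add rows to Table 1, in both arms, at the operation/month 0 column and at month 3, for ureteral injury, intraoperative bleeding or transfusion, and pelvic collection or infection or flap necrosis. The data can come from operative and discharge notes.
- State in item 21b that these events, with the three complications already named, are among those compared between arms at the interim.

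The cost is a few case report form items, a wording amendment and a less favourable stated risk profile.
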